# SYNOPSIS

## *Title*

Evaluation of 4 artemisinin-based combinations for treating uncomplicated malaria in African children

## *Methodology*

A multicentre, phase IV, randomized, open label, multi-arm study. Each patient will be actively followed for 28 days and then passively until 6 months after treatment. If, during the passive follow up, the patient experiences a second uncomplicated malaria episode, s/he will be treated with the same drug and actively followed up for additional 28 days.

### Follow up chart first and second active follow up.

| Day                     | 0              | 1              | 2              | 3 | 4              | 5              | 6              | 7 | 14             | 21 | 28 | Any other day  |
|-------------------------|----------------|----------------|----------------|---|----------------|----------------|----------------|---|----------------|----|----|----------------------------|
| History (symptoms)      | X              |                |                |   |                |                |                | X | X              | X  | X  | X                          |
| Informed consent        | X  |                |                |   |                |                |                |   |                |    |    |                            |
| Examination (clinical)  | X              | X              | X              | X |                |                |                | X | X              | X  | X  | X                          |
| Temperature             | X              | X              | X              | X |                |                |                | X | X              | X  | X  | X                          |
| Blood film              | X              | X              | X              | X |                |                |                | X | X              | X  | X  | X                          |
| Filter paper PCR        | X              | X              |                |   |                |                |                |   | X              | X  | X  | X                          |
| Adverse drug reactions  | X              | X              | X              | X | X  | X  | X  | X | X              | X  | X  | X                          |
| Concomitant medications | X              | X              | X              | X |                |                |                | X | X              | X  | X  | X                          |
| Haematology             | X              | X  | X  | X |                |                |                | X | X              |    | X  | X                          |
| Biochemistry            | X              |                |                |   |                |                |                | X | X  |    | X  |                            |
| Treatment               | X              | X              | X              |   |                |                |                |   |                |    |    |                            |

 Spontaneous attendance to health facility;  Only at the beginning of the first follow up.  In sites where CDA is tested, Hb will be determined also at day 1 and 2 after treatment and for the three arms of the study;  If abnormal at day 7.  If patient attends spontaneously the health facility.

**Study Duration**  
Calendar of activity.

| YEAR                                                   | 1 |   |   |   | 2 |   |   |   | 3 |   |   |   |
|--------------------------------------------------------|---|---|---|---|---|---|---|---|---|---|---|---|
| QUARTERS                                               | 1 | 2 | 3 | 4 | 1 | 2 | 3 | 4 | 1 | 2 | 3 | 4 |
| Preparatory phase                               |   |   |   |   |   |   |   |   |   |   |   |   |
| Meeting of research groups (coordination)              |   |   |   |   |   |   |   |   |   |   |   |   |
| Production of final detailed protocol                  |   |   |   |   |   |   |   |   |   |   |   |   |
| CRF and data base design                               |   |   |   |   |   |   |   |   |   |   |   |   |
| Ethical Committee approval                             |   |   |   |   |   |   |   |   |   |   |   |   |
| Information/agreement with study populations           |   |   |   |   |   |   |   |   |   |   |   |   |
| Training in GCP                                        |   |   |   |   |   |   |   |   |   |   |   |   |
| Training data entry and data management                |   |   |   |   |   |   |   |   |   |   |   |   |
| Implementation phase                            |   |   |   |   |   |   |   |   |   |   |   |   |
| Coordination meetings (teleconferences every 3 months) |   |   |   |   |   |   |   |   |   |   |   |   |
| Monitoring initiation visit                            |   |   |   |   |   |   |   |   |   |   |   |   |
| Recruitment of patients                                |   |   |   |   |   |   |   |   |   |   |   |   |
| (Second) Follow-up                                     |   |   |   |   |   |   |   |   |   |   |   |   |
| Monitoring visits (3 times per site)                   |   |   |   |   |   |   |   |   |   |   |   |   |
| Closure monitoring visit                               |   |   |   |   |   |   |   |   |   |   |   |   |
| Interim analysis                                       |   |   |   |   |   |   |   |   |   |   |   |   |
| Genotyping blood samples                               |   |   |   |   |   |   |   |   |   |   |   |   |
| Data Analysis                                          |   |   |   |   |   |   |   |   |   |   |   |   |
| Publications                                           |   |   |   |   |   |   |   |   |   |   |   |   |

**Countries**

7 African countries: Burkina Faso, Nigeria, Gabon, Uganda, Mozambique, Zambia, Rwanda.

**Study Center(s)**

10 sites

**Objectives**

The main objective is to compare the safety and efficacy of 4 artemisinin-based combinations (ACT) [amodiaquine-artesunate (AQ+AS), dihydroartemisinin-piperaquine (DHAPQ), artemether-lumefantrine (AL) and chlorproguanil/dapsone-artesunate (CDA)] for single and repeat treatments of uncomplicated malaria in children. Safety will be determined by registering adverse events and grading, laboratory, and vital signs evaluations. Their incidence will be compared between the different study arms.

Specific objectives are the following:

1. To evaluate the efficacy of the 4 ACTs for the treatment of children with uncomplicated *P. falciparum* malaria (first active follow-up);
2. To determine after the first active follow-up the incidence rate of a second clinical episode of uncomplicated *P. falciparum* malaria;
3. To evaluate the efficacy of treating the second clinical episode of uncomplicated *P. falciparum* malaria with the same ACT used for the first one (second active follow-up);
4. To evaluate during the active and passive follow up the safety of the 4 ACTs for the treatment of children with uncomplicated *P. falciparum* malaria;

- To establish the impact of using CDA on the selection of *P. falciparum* genotypes linked to SP resistance.

### **Number of Subjects**

170 patients/arm/site, 510 patients/site, 5100 in total. The total number of patients treated by each study drug will be more than 1000. For the direct comparisons between treatment arms, the highest number of patients per arm will be 1360 (DHAPQ vs AL), and the lowest 340 for the direct comparison between AQ+AS and CDA. (see table below).

### **Study treatment to be tested by country and institutions.**

| Country      | Numb. sites | Affiliation       | Study treatments |       |       |
|--------------|-------------|-------------------|------------------|-------|-------|
| Burkina Faso | 1           | Centre Muraz/IRSS | AQ+AS            | DHAPQ | AL    |
| Nigeria      | 1           | TDRI              | AQ+AS            | DHAPQ | AL    |
| Zambia       | 1           | TDRC              | AQ+AS            | DHAPQ | AL    |
| Gabon        | 1           | HAS/Tubingen      | AQ+AS            | DHAPQ | AL    |
| Uganda       | 2           | EANMAT            | DHAPQ            | CDA   | AL    |
| Uganda       | 1           | EPICENTRE         | AQ+AS            | CDA   | DHAPQ |
| Rwanda       | 2           | EANMAT            | DHAPQ            | CDA   | AL    |
| Mozambique   | 1           | Manhiça           | AQ+AS            | CDA   | DHAPQ |

CQR: Chloroquine resistance; SPR: sulfadoxine-pyrimethamine resistance; AQ+AS: amodiaquine-artesunate; DHAPQ: dihydroartemisinin-piperaquine; AL: artemether-lumefantrine; CDA: chlorproguanil-dapsone-artesunate;

### **Diagnosis and Main Inclusion Criteria**

Children 6-59 months old (this criterion applies only for the first active follow up) (in sites testing CDA the age group for the 3 study arms will be 12-59 months) with suspected uncomplicated clinical malaria attending the health facility where the study is carried out will be recruited into the study and randomised to one of the study treatments if they fulfil all the following inclusion criteria: 1. Weight > 5 kg; 2. Mono-infection with *P. falciparum* and a parasitaemia of 2,000–200,000 asexual parasites per µl; 3. Fever (axillary temperature ≥37.5 °C) or history of fever in the preceding 24 hours; 4. Haemoglobin value ≥ 7.0 g/dl; 5. Signed informed consent by the parents or guardians; 6. Parents' or guardians' willingness and ability to comply with the study protocol for the duration of the trial.

They will be excluded if they have at least one of the following criteria:

- Participation in any other investigational drug study (antimalarial or others) during the previous 30 days
- Known hypersensitivity to the study drugs
- Severe malaria\*.
- Danger signs: not able to drink or breast-feed, vomiting (> twice in 24hours), recent history of convulsions (>1 in 24h), unconscious state, unable to sit or stand;
- Presence of intercurrent illness or any condition (cardiac, renal, hepatic diseases) which would place the subject at undue risk or interfere with the results of the study, including known G6PD deficiency.
- Severe malnutrition (defined as weight for height <70% of the median NCHS/WHO reference)
- Ongoing prophylaxis with drugs having antimalarial activity such as cotrimoxazole for the prevention of *Pneumocystis carinii* pneumonia in children born to HIV+ women.

\*WHO 2000: Severe falciparum malaria. *Trans. R. Soc. Trop. Med. Hyg.* **94**, 1-90.

Children infected with other malaria species and those with mixed malaria infections will be excluded from the study but adequate treatment will be provided. Cases of severe and complicated malaria will be referred to hospital for treatment with intravenous quinine and other supportive therapy.

### ***Study endpoints***

#### **Primary end points**

1. PCR unadjusted treatment failure (TF28U): all treatment failures detected during the active follow up, regardless of genotyping.
2. PCR adjusted treatment failure up to day 28 (TF28A): all early failures before day 14 plus the recurrent parasitaemias detected at day 14 or later and classified by genotyping as recrudescence.

#### **Secondary endpoints (first and second active follow-up)**

- PCR unadjusted treatment failure up to day 63 (TF63U): TF28U plus all cases of recurrent parasitaemia (symptomatic or asymptomatic) detected between day 29 and day 63 by passive follow up, regardless of genotyping
- PCR adjusted treatment failure for the whole period of passive surveillance (TFAPS): TF28A plus all episodes of recurrent parasitaemia identified as recrudescence by genotyping.
- Fever clearance time.
- Asexual parasite clearance time.
- Gametocytaemia (prevalence and density) at day 7, 14, 21 and 28 after treatment (for both active follow-ups);
- Hb changes day 3, 7, 14 and 28 (first and second follow up);
- Clinical malaria after first active follow-up;
- Clinical malaria after second active follow-up;
- TF second clinical episode (D28 and D63);
- Changes in the frequency of mutations in the dihydrofolate reductase (DHFR) gene at day 0 first follow-up and day re-appearance of parasitaemia (for patients treated with CDA).
- Safety profiles including significant changes in relevant laboratory values.

### **Statistical analysis**

For the proposed trials each pairwise comparison of treatments will be considered, stratified by site. Heterogeneity due to patient-level and site-level characteristics will be investigated. Finally, all data will be entered into a regression model and a network meta-analytic approach adopted. For each pairwise comparison, both an intention-to-treat, a per-protocol and a Compliance Adjusted Causal Effect (CACE) approach will be adopted. Within each site patients in each treatment group will be described separately with respect to baseline characteristics. The clinical importance of any imbalance will be noted though statistical tests of significance will not be undertaken. For treatment failure, the relative treatment effect will be summarised in terms of the odds ratio and confidence interval, provided no significant unexplained heterogeneity is evident on this scale. If appropriate, logistic regression will be

---

 Lumley T. Network meta-analysis for indirect treatment comparisons. *Statistics in Medicine* 2002; 21: 2313-2324.

used to examine the effect of prognostic factors on this outcome. Tests of interaction between baseline characteristics and treatment will be kept to a minimum. Adverse events will be grouped according to a pre-specified side-effect coding system and tabulated. The number (and percentage) of patients experiencing each adverse event will be compared across treatment groups. The number (and percentage) of occurrences of each adverse event will also be compared across treatment groups. No formal statistical testing will be undertaken.

Every effort will be made to minimise the amount of missing data in the trial. However it is realistic to assume a priori that missingness may be informative. Whenever possible, information on the reason for missing data will be obtained. Sensitivity analyses, including imputation, will be considered to assess the robustness of the conclusions to the missing data.

Interim analyses will be undertaken by the trial statistician and presented to the DSMB every six months during recruitment, i.e. approximately after every 500 patients per group have been entered. A detailed analysis plan will be drawn up prior to the first interim analysis.

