### **3.5 Sample size**

Sample size is estimated according to the expected efficacy at day 28 after treatment as in Africa there is no information beyond this point. Efficacy of each study treatments is likely to be at least 90%. A sample of 155 children per arm will be able to show, in each site, at the 5% significance level with 90% power, that the difference in efficacy between treatments is not more than 10%. Allowing for a loss to follow-up around 10%, the final sample size per arm will be 170 children. Moreover, when combined, the studies will be able to detect a significant difference in efficacy between treatments of 4-6% and major adverse events occurring at the frequency of at least 1-2%.

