### **3.6 Statistical analysis**

Since the trial has been powered for equivalence at each site, interim analyses will be undertaken for each of the sites separately. Interim analyses will be undertaken by the trial statistician and presented to the DSMB every 6 months during recruitment while safety monitoring will be continuous. A detailed analysis plan will be drawn up prior to the first interim analysis.

For each analysis, both an intention-to-treat, a per-protocol and a CACE approach will be adopted. Patients in each treatment group in each site will be described separately with respect to baseline characteristics. The clinical importance of any imbalance will be noted though statistical tests of significance will not be undertaken.

For the analysis at each site, and for the primary outcomes relating to treatment failure, the relative treatment effect will be summarised in terms of the risk difference and associated confidence interval for each pairwise combination of treatments.

For the combination of data across sites, a meta-analytic approach will be employed. The six pairwise comparisons of treatments will be undertaken, stratified by site. Heterogeneity due to patient-level and site-level characteristics will be investigated. Finally, all data will be entered into a regression model and a network meta-analytic approach adopted.

If appropriate, logistic regression will be used to examine the effect of prognostic factors on the primary outcome. Tests of interaction between baseline characteristics and treatment will be kept to a minimum.

Adverse events will be grouped according to a pre-specified side-effect coding system and tabulated. The number (and percentage) of patients experiencing each adverse event will be compared across treatment groups. The number (and percentage) of occurrences of each adverse event will also be compared across treatment groups.

Every effort will be made to minimise the amount of missing data in the trial. However it is realistic to assume a priori that missingness may be informative. Whenever possible, information on the reason for missing data will be obtained. Sensitivity analyses, including imputation, will be undertaken to assess the robustness of the conclusions to the missing data.

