### ***3.11 Randomisation and treatment allocation***

A randomisation list of blocks of varying size and stratified according to the number of recruitment points in each site will be provided by the Centre for Medical Statistics and Health Evaluation/ University of Liverpool. Sealed envelopes labelled with the patients unique code and containing the treatment allocated to the patient will also be provided by Liverpool according to the above mentioned list. This will guarantee concealment as the envelope will be opened only after recruitment.

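### The pooled effect scale for treatment failure is not settled: the synopsis gives an odds ratio conditional on heterogeneity, section 3.6 a risk difference for sites only, while the design aims are absolute differences

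*Protocol*

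**What the plan says.** The relevant text stands in four places in the protocol.

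- **Synopsis, Statistical analysis.** After describing pairwise comparisons stratified by site and a network meta-analysis, it says for treatment failure that "the relative treatment effect will be summarised in terms of the odds ratio and confidence interval, provided no significant unexplained heterogeneity is evident" on that scale. The sentence is not limited to site or pooled results, and no other measure is named for the case where heterogeneity is found.
- **Section 3.6.** "For the analysis at each site, and for the primary outcomes relating to treatment failure", the effect is to be "summarised in terms of the risk difference and associated confidence interval for each pairwise combination of treatments". It continues: "For the combination of data across sites, a meta-analytic approach will be employed", and "The six pairwise comparisons of treatments will be undertaken, stratified by site". A network regression follows. No effect scale is named for the combined data.
- **Section 3.5.** With 155 children per arm, each site is to show "that the difference in efficacy between treatments is not more than 10" percent. Combined, the studies are to detect differences in efficacy of 4-6%.
- **Section 3.11.** The randomisation list is "stratified according to the number of recruitment points in each site". Neither analysis text mentions recruitment point.

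**The concern.** Synopsis and section 3.6 give different measures for the same outcome, and neither states which governs the pooled result. That result is the one most likely to be cited for policy across seven countries.

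Both aims in section 3.5 are absolute differences. An odds ratio converts to an absolute difference only through the baseline failure risk, and that risk should be expected to differ between sites. Table 1 lists entomological inoculation rates from 6 to above 70 and varying drug resistance, and the first primary endpoint (PCR-unadjusted failure, section 3.2) counts new infections.

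The condition in the synopsis adds a second gap. If heterogeneity is significant, the stated summary lapses and nothing replaces it. The rule would also act unevenly: in Table 1, AQ+AS and CDA meet directly at two sites (one degree of freedom for heterogeneity), DHAPQ and AL at eight.

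**Working it through.** **1. Scale of the design.** Inputs from section 3.5: efficacy 90% in both arms, margin 10 points, 5% significance, 90% power. The sidedness is not stated; one-sided 5% is assumed here.

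n per arm = 2 × 0.9 × 0.1 × (1.645 + 1.282)² / 0.10² = 0.18 × 8.564 / 0.01 = 154.2, rounded up to 155.

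This reproduces the protocol's figure exactly (one-sided 2.5% would give 190). The design is therefore on the risk-difference scale, and the site-level risk difference in section 3.6 agrees with it.

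**2. What 10 points means as an odds ratio.** With p the failure risk in the reference arm, OR = [(p + 0.1)/(0.9 − p)] / [p/(1 − p)]. In the other direction, an odds ratio of 2.25 gives a difference of 2.25p/(1 − p + 2.25p) − p. Only p = 10% is a planning value of the protocol; the other risks are assumptions.

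| Reference failure p | OR equal to 10 points | Points implied by OR 2.25 |
|---|---|---|
| 5% | 3.35 | 5.6 |
| 10% | 2.25 | 10.0 |
| 20% | 1.71 | 16.0 |
| 30% | 1.56 | 19.1 |

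**3. The same for the pooled aim.** With d the difference, OR = [(p + d)/(1 − p − d)] / [p/(1 − p)].

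| p | OR at 4 points | OR at 6 points |
|---|---|---|
| 5% | (0.09/0.91)/(0.05/0.95) = 1.88 | (0.11/0.89)/(0.05/0.95) = 2.35 |
| 10% | (0.14/0.86)/(0.10/0.90) = 1.47 | (0.16/0.84)/(0.10/0.90) = 1.71 |
| 20% | (0.24/0.76)/(0.20/0.80) = 1.26 | (0.26/0.74)/(0.20/0.80) = 1.41 |

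An odds ratio of 1.71 is 6 points at 10% failure and 10 points at 20%. No single pooled odds ratio corresponds to either stated aim.

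**4. Recruitment point.** Assume two equal-sized points with failure risks p1 and p2. Compare the mean of p(1 − p) within points with the value at the average risk.

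| p1, p2 (assumed) | Within points | Ignoring points | Variance falls by | CI narrows by |
|---|---|---|---|---|
| 5%, 15% | (0.0475 + 0.1275)/2 = 0.0875 | 0.10 × 0.90 = 0.0900 | 2.8% | 1.4% |
| 5%, 20% | (0.0475 + 0.16)/2 = 0.1038 | 0.125 × 0.875 = 0.1094 | 5.1% | 2.6% |
| 10%, 40% | (0.09 + 0.24)/2 = 0.1650 | 0.25 × 0.75 = 0.1875 | 12% | 6.2% |

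The last column is 1 minus the square root of the variance ratio. The third row is extreme against a planned failure of about 10%.

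**The case against.** The strongest reply is that the two texts can be reconciled. Section 3.6 confines the risk difference to each site. The synopsis odds ratio follows text on site-stratified and network comparisons, so it can be taken as the pooled measure. That reading is reasonable, but neither place states it, so the ambiguity remains.

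It can also be said that the pooled aim is to detect a difference, and an odds ratio of 1 and a risk difference of 0 are the same null. This is right for the test. It does not help with the size of the effect, which section 3.5 gives in points.

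An odds ratio may also be the more stable scale across sites. Table 2 of the working points (constant odds ratio, 5.6 to 19.1 points) shows how a single pooled risk difference could be heterogeneous where the odds ratio is not. This stands, and is why the odds ratio should be kept rather than replaced.

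Several stronger readings are tempting but unsupported:

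- A reader might infer that the site result does not match its margin. It does: both are risk differences, and 155 per arm reproduces on that scale.
- A reader might infer that the randomisation strata are ignored altogether. Both analysis texts stratify by site; only recruitment point within site is absent. Section 3.11 does not say how many points each site has, and such detail may stand in the analysis plan, which was not available here.
- A reader might infer that the site analysis is fixed as unadjusted. Section 3.6 does not say so, and it allows logistic regression for prognostic factors.
- A reader might infer that the scale will be picked from the data. The synopsis names no second scale; the clause may only mean that a single summary is withheld when sites disagree. The fault is the missing fallback.

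**Conclusion.** The point holds for the pooled and network results. The protocol does not settle their effect scale, it makes the one measure it names conditional on a heterogeneity finding without a fallback, and an odds ratio alone cannot be set against aims stated in percentage points. The odds ratio equal to 10 points runs from 3.35 to 1.71 as reference failure goes from 5% to 20%, around 2.25 at the planned 10%. The range rests on assumed site risks; that they differ is likely from Table 1 but is not quantified in the protocol.

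Recruitment point is a minor addition. Leaving it out makes intervals slightly too wide, not invalid: about 3-5% of variance under moderate assumed differences, 12% only in an extreme case. Neither matter changes the sample size.

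**What to change.** 1. Align the synopsis with section 3.6: the risk difference with confidence interval is the site-level measure in both.
2. For pooled pairwise and network results, state that the absolute risk difference with confidence interval is reported alongside the odds ratio. It may be derived from the odds-ratio model.
3. Replace the heterogeneity condition in the synopsis with unconditional reporting of the effect and a description of heterogeneity between sites.
4. Where a site has more than one recruitment point, stratify the site and pooled analyses by recruitment point within site, for example by Mantel-Haenszel, to match section 3.11.

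The cost is a change of wording and slightly more programming. The 155 and 170 per arm stand, and no new data are needed beyond each child's recruitment point, which the randomisation list already defines.

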## 2. TRIAL OBJECTIVES AND PURPOSE

The main objective is to compare the safety and efficacy of 4 artemisinin-based combination therapies (ACT), i.e. amodiaquine-artesunate (AQ+AS), artemether-lumefantrine (AL), dihydroartemisinin-piperaquine (DHAPQ), chlorproguanil-dapsone-artesunate (CDA), for single and repeat treatments of uncomplicated malaria in African children. Safety will be determined by registering adverse events and grading, laboratory, and vital signs evaluations. Their incidence will be compared between the different study arms.

Specific objectives are the following:

1. To evaluate the efficacy of the 4 ACTs for the treatment of children with uncomplicated *P. falciparum* malaria (first active follow-up);
2. To determine after the first active follow-up the incidence rate of a second clinical episode of uncomplicated *P. falciparum* malaria;
3. To evaluate the efficacy of treating the second clinical episode of uncomplicated *P. falciparum* malaria with the same ACT used for the first one (second active follow-up);
4. To evaluate during the active and passive follow up the safety of the 4 ACTs for the treatment of children with uncomplicated *P. falciparum* malaria;
5. To establish the impact of using CDA on the selection of *P. falciparum* genotypes linked to SP resistance.

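### Safety is part of the main objective, but the protocol plans only counts and percentages of adverse events across treatment groups and names no site-stratified estimate or interval for any harm

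*Protocol*

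**What the plan says.** The synopsis (Objectives) and section 2 set one main objective: to compare both the safety and the efficacy of the four combinations. On adverse events and the other safety evaluations they add: "Their incidence will be compared between the different study arms".

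The analysis is described twice:

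- **Synopsis, Statistical analysis.** Adverse events are coded and tabulated. "The number (and percentage) of patients experiencing each adverse event will be compared across treatment groups". Occurrences are handled likewise, and the paragraph ends: "No formal statistical testing will be undertaken".
- **Section 3.6.** The same paragraph appears, including "The number (and percentage) of occurrences of each adverse event will also be compared across treatment groups", but the closing sentence on testing is absent.

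Confidence intervals are named only for treatment failure (odds ratio in the synopsis, risk difference in section 3.6).

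Section 3.5 says the combined studies will be able to "detect a significant difference in efficacy between treatments of 4-6" percent and, in the same sentence, "major adverse events occurring at the frequency of at least 1-2" percent. It gives no comparator rate, significance level or power for the second part.

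Section 3.1 puts the direct comparisons at 340 to 1360 patients per arm. Table 1 shows which three drugs each site tests. Section 3.9 sets the age range at 6 to 59 months, or 12 to 59 months in all arms at sites testing CDA.

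**The concern.** Three things come together.

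1. The two descriptions differ on whether adverse events may be tested. An analysis plan that tested a harm would follow section 3.6 and contradict the synopsis.
2. The only planned output for harms is a table across treatment groups. The four groups were not recruited at the same places or over the same age range, so a difference between overall totals is not purely a randomised comparison.
3. The direct pairs differ fourfold in size, so the same pair of percentages carries very different evidence. A reader would have to work that out from the counts.

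At stake is how firmly the trial can report on safety, including the haemolysis and haemoglobin falls that sections 1.1 and 14 raise for chlorproguanil-dapsone.

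**Working it through.** **Reproducing the plan's own figures.** Table 1, at 170 children per arm per site:

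- Four sites test AQ+AS, DHAPQ and AL; four test DHAPQ, CDA and AL; two test AQ+AS, CDA and DHAPQ.
- Totals: DHAPQ 10 × 170 = 1700; AL 8 × 170 = 1360; AQ+AS 6 × 170 = 1020; CDA 6 × 170 = 1020.
- Direct pairs, per arm: DHAPQ v AL 8 × 170 = 1360; DHAPQ v AQ+AS and DHAPQ v CDA 6 × 170 = 1020 each; AL v AQ+AS and AL v CDA 4 × 170 = 680 each; AQ+AS v CDA 2 × 170 = 340.

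These match section 3.1. The per-site 155 in section 3.5 also reproduces, as 2 × 0.9 × 0.1 × (1.645 + 1.282)² / 0.10² = 154.2, rounded up. That calculation concerns efficacy only.

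**How far the groups differ in site and age.** The four sites without CDA recruit from 6 months and the six CDA sites from 12 months. The share of each drug's children coming from sites without CDA is:

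- AQ+AS 680/1020 = 67%
- AL 680/1360 = 50%
- DHAPQ 680/1700 = 40%
- CDA 0/1020 = 0%

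Illustration (assumed rates): suppose an event occurs in 3% of children at sites without CDA and 1% at CDA sites, whatever the drug. The overall totals would then be:

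- AQ+AS (20.4 + 3.4)/1020 = 2.33%
- AL (20.4 + 6.8)/1360 = 2.00%
- DHAPQ (20.4 + 10.2)/1700 = 1.80%
- CDA 10.2/1020 = 1.00%

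AQ+AS and CDA would differ by 1.33 points with no drug effect. If the two site rates were swapped, the sign would reverse. A comparison stratified over the two sites that randomise both drugs would centre on zero in either case.

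**Precision across the direct pairs.** SE = √[p₁(1−p₁)/n + p₂(1−p₂)/n], interval = difference ± 1.96 SE. For an assumed 3% v 1%, the numerator is 0.0291 + 0.0099 = 0.039.

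| n per arm | half-width (points) | 95% CI (points) | z |
|---|---|---|---|
| 340 | 2.10 | -0.10 to 4.10 | 1.87 |
| 680 | 1.48 | 0.52 to 3.48 | 2.64 |
| 1020 | 1.21 | 0.79 to 3.21 | 3.23 |
| 1360 | 1.05 | 0.95 to 3.05 | 3.73 |

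For an assumed 2% v 1%, the interval is about -0.8 to 2.8 at 340 and 0.1 to 1.9 at 1360.

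**What *detect* in section 3.5 could mean.**

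- *Observing at least one event in an arm:* 1 − (1 − p)ⁿ. At p = 1% this is 96.7% with 340 children and over 99.99% with 1020. At p = 2% it is 99.9% with 340. The statement is then true and needs no test.
- *Showing a between-arm difference (two-sided 5%, comparator rates assumed):* 1% v 2% has 19% power at 340 per arm and 57% at 1360. A near-zero rate (0.01%) v 1% has 45% at 340, 88% at 1020 and 95% at 1360. The statement then holds only against a near-zero comparator and in the larger pairs.

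**The case against.** The case against making much of this is substantial.

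- **A ban on tests is not a ban on intervals.** A reader might infer that safety will end with no measure of uncertainty. The sentence does not say so, and an analysis plan could add intervals without contradicting it. This stands.
- **Section 3.5 states no power for adverse events.** A reader might infer a promised between-arm test that no analysis supports. The word difference is attached to efficacy, and the adverse-event part can be read as observing events, which the sample sizes allow. This stands; the wording is only ambiguous.
- **The table gives counts as well as percentages.** A reader might infer that a small and a large comparison would look the same. At 3% v 1% the counts would be about 31 v 10 with 1020 per arm and 10 v 3 with 340, and an interval could be computed from them. This stands.
- **Haemoglobin change is a separate secondary endpoint** (section 3.3), so it is not clearly governed by the sentence on testing. The protocol names haemolysis and haemoglobin falls for chlorproguanil-dapsone. It lists severe anaemia only as a criterion for severe malaria (Appendix V). This stands.
- **Safety is listed as a secondary endpoint, and descriptive tables are a common and defensible choice** when many event types are reported. Safety monitoring is continuous, and an independent board can stop arms. Further detail may properly sit in the analysis plan. This largely stands.
- **Site-stratified pairwise comparisons are already planned**, and the sentence introducing them is not expressly limited to efficacy. This stands in part: the adverse-event paragraph that follows does not invoke them and describes only tabulation across treatment groups.

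The objections leave untouched the mismatch between the two descriptions and the mixing of site and age in overall totals.

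**Conclusion.** The point holds as a modest, inexpensive improvement. The synopsis and section 3.6 do not agree on testing, since one forbids it and the other is silent. For an aim that is part of the main objective, no between-arm estimate or interval is named for any harm. Site-stratified risk differences are a better method here than totals across treatment groups, because drug is tied to site and age range by design. Between 0% and 67% of a drug's children come from the sites recruiting from 6 months.

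The site and age shares and the pair sizes follow from the protocol alone. The 1.33-point spurious difference and the interval widths rest on assumed event rates, since the protocol gives none. Between 340 and 1360 per arm, though, half-widths differ by a factor of two (√4) at any fixed pair of rates.

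The documents do not support the stronger conclusion that the safety objective cannot be answered.

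**What to change.** 1. Make the synopsis and section 3.6 agree. The no-testing sentence may stay, in both places, for the general adverse-event tables.
2. Name a short list of key harms in advance, for example any serious adverse event, a haemoglobin fall of at least 2 g/dL, and haemoglobin below 5 g/dL. For each, report the risk difference with its 95% confidence interval for every direct pair, stratified by site over the sites that randomised both drugs. Label these as estimation without multiplicity adjustment.
3. In section 3.5, say whether *detect* means observing at least one event at a 1-2% frequency or showing a between-arm difference. If the latter, give the comparator rate, significance level and power.

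The cost is wording in the protocol or analysis plan and a few estimates from data already collected, with no added patients or visits. The downside is small: several unadjusted intervals will be read side by side, which is why the label is needed.
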